### Measures: Predictor Variables

#### Demographic Variables

Although support for demographic variables and their relationship to treatment adherence varies, a host of demographic variables will be included as candidate predictor variables. Predictor variables include race, ethnicity, household income, age, gender, as well as identifying as a same-gender couple.

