#### Baseline Measures of Relationship and Individual Symptomology

In line with the consistencies in previous research and in addition to relationship satisfaction, several measures of relationship symptomology will be used as possible candidates to predict program completion and gains in relationship satisfaction.

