#### Measures of External Stress

##### Overview

In addition to including predictors of relationship well-being, the inclusion of measures assessing external stress has been shown to be a consistent predictor of treatment adherence. In addition, as this is measured at the individual level, this may highlight within-relationship differences that may aid in the prediction of treatment nonadherence and satisfaction gains. This study intends to measure psychological distress and general health using the following measures:

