#### Measures of Motivation

A final category of predictors of treatment adherence is the motivation to complete the treatment. In line with the literature, motivation will be measured using grit and motivation to change.

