#### Data Analysis Plan for Aim 1: Examining the Prediction Accuracy of the Within-Group Models Using the Random Forest Algorithm

The first research question asks: how well can one predict program completion and anticipated gains within (1) the full-coach condition, (2) the automated coach condition, and (3) the contingent coach condition? To ensure that the different programs do not account for a substantial portion of the variance when predicting program completion or changes in relationship satisfaction, a test will be performed where 2 models will be created and compared. In the first model, all predictors will be interacted with the level of coaching (full, contingent, and automated) and the program assignment (ie, OurRelationship and ePREP) resulting in Predictor×Treatment×Coaching interactions. However, the second model will maintain all predictors by coaching interactions but drop all program assignment interactions (ie, resulting in only Predictor×Coaching interactions). Next, the root mean square error (RMSE) between the 2 models will be compared. If the null hypothesis does not get rejected (H_0_: RMSE_Model 1_ = RMSE_Model 2_), program assignment will be ignored resulting in 3 conditions (full, contingent, and automated coaching), which will be used in the proceeding aims. If the interactions account for a significant portion of the variance (H_a_ = RMSE_Model 1_ ≠ RMSE_Model 2_), independent models will be built by treatment (ie, OurRelationship or ePREP) and coach condition (full, automated, and contingent) resulting in 6 models: OurRelationship full coach, OurRelationship automated coach, OurRelationship contingent coach, ePREP full coach, ePREP automated coach, and ePREP contingent coach, which will be used in the proceeding aims.

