#### Data Analysis Plan for Aim 2: What Are the Most Important Within-Group Predictors?

The second research question is: what are the most powerful predictors of treatment adherence and gains in relationship satisfaction within (1) the full-coach condition, (2) the automated coach condition, and (3) the contingent coach condition? If, in aim 1, the interaction terms result in a lower RMSE, better sensitivity, or better specificity, models will be constructed based on treatment assignment (ie, OurRelationship or ePREP) and coach assignment (ie, full, contingent, or automated). One statistically powerful way to test the most potent predictors of treatment adherence and gains is through the use of variable importance (VIMP). VIMP is a nonparametric approach within the random forest algorithm, which can help investigators identify which variables play a key role in predicting a binary (eg, program completion) or continuous (eg, improvements in relationship satisfaction) variable [53]. VIMP has been calculated in many ways in the past; however, one way that has shown promise has been through permutation (ie, Briemen–Cutler) importance [53]. This method randomly changes a given variable’s out-of-bag data and compares and averages the permuted prediction error with the original error resulting in VIMP [53]. This process not only helps identify which variables play a key role in prediction but also overcomes issues of overtesting using bootstrapping. Recent studies have used these out-of-bag estimates to generate CIs to test whether a variable has a meaningful effect in predicting an outcome with great success [53]. Indeed, these studies have suggested that 95% CIs that do not include zero will be assumed to have reliable predictors [53]. After identifying the most powerful predictors using VIMP, a multiple regression model will be estimated using the reduced set of variables to aid in the interpretation of the main effects, helping clinicians identify predictors of treatment adherence and gains.

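### Aim 2 says bootstrapping takes care of overtesting, but its rule for a reliable predictor is an unadjusted 95% interval applied about 114 (or 228) times

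*Protocol article*

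**What the plan says.** The protocol article's data analysis plan for Aim 2 uses Breiman–Cutler permutation VIMP from a random forest to find the strongest predictors of program completion and of satisfaction gains. It makes two statements that matter here. The first is that the procedure "also overcomes issues of overtesting using bootstrapping". The second, attributed to recent studies, is the decision rule: "95% CIs that do not include zero will be assumed to have reliable predictors". The section mentions no adjusted level, false-discovery control or ordering of hypotheses. Predictors identified by VIMP then enter a multiple regression intended to help clinicians interpret the effects.

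The aims and hypotheses section uses the same vocabulary. It predicts that lower external stress and higher intrinsic motivation will prove reliable predictors of adherence and gains, whatever the coaching assignment.

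**The concern.** Resampling shows how much one VIMP varies from sample to sample, and out-of-bag evaluation keeps a forest from being scored on its own training data. Neither takes account of how many VIMPs are inspected. A 95% interval applied separately to each predictor, outcome and model keeps its per-interval error rate, so expected false flags grow in proportion to the number of intervals.

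This is more than detail left to a later document. The article says the problem is already solved, which tells whoever writes the preregistration that no correction is needed. At stake is which predictors are called reliable and carried into the regression meant for clinicians.

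**Working it through.** The article gives no number of intervals and no error rate, so there is no figure of its own to reproduce. The count below is built from its lists.

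**Predictors**
- Demographic, 6: "Predictor variables include race, ethnicity, household income, age, gender, as well as identifying as a same-gender couple".
- Relationship, 7: "in addition to relationship satisfaction, several measures of relationship symptomology will be used as possible candidates". These are baseline satisfaction plus breakup potential, commitment, biggest problem, communication conflict, emotional support and intimate partner violence.
- External stress, 4: psychological distress, perceived stress, chaos, general health.
- Motivation, 2: "motivation will be measured using grit and motivation to change".

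Total: 6 + 7 + 4 + 2 = 19.

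**Outcomes:** 2 (completion and satisfaction gain).

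**Models:** 3 if the Aim 1 comparison lets program be ignored, 6 if it does not.

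**Intervals:** 19 × 2 × 3 = 114, or 19 × 2 × 6 = 228. These are two alternative scenarios, not the ends of a range. The tally depends on couple-level coding that the article does not give. Dropping gender, for example, gives 18 × 2 × 3 = 108 or 18 × 2 × 6 = 216.

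**Expected false flags** = intervals × share null × error per interval. A calibrated 95% interval excludes zero on the positive side 2.5% of the time under the null, and on either side 5% of the time. A useful predictor has positive VIMP, so the positive-side columns are the more natural reading. The share of null predictors is not known and is varied as an assumption.

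| Share null | 114, positive only | 114, both sides | 228, positive only | 228, both sides |
|---|---|---|---|---|
| All | 2.85 | 5.7 | 5.7 | 11.4 |
| Three quarters | 2.14 | 4.28 | 4.28 | 8.55 |
| Half | 1.43 | 2.85 | 2.85 | 5.7 |
| One quarter | 0.71 | 1.43 | 1.43 | 2.85 |

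**Chance of at least one false flag, all null and independent:** 1 − 0.975^114 = 0.944 and 1 − 0.975^228 = 0.997 on the positive side; 1 − 0.95^114 = 0.997 and 1 − 0.95^228 > 0.999 on both sides. Correlation among predictors changes these probabilities but not the expected counts.

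**Calibration.** The article does not specify how the VIMP intervals are formed. A small null simulation (288 couples, 19 noise predictors, subsampling-based intervals, 14 replicates) gave positive-side false-flag rates from about 0.4% to about 5% per interval, depending on subsample size and centring. That is roughly 0.4 to 6 of 114, or 0.9 to 12 of 228. It is indicative only, but it shows that the nominal 2.5% cannot be taken for granted in either direction.

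**The stated hypothesis.** It has to hold at every coaching level. For one outcome, with independent arms and the positive side only, a given null predictor passes in all three arms with probability 0.025^3 ≈ 0.00002. If any one of the four stress measures suffices in each arm, the probability is (1 − 0.975^4)^3 ≈ 0.0009, or (1 − 0.95^4)^3 ≈ 0.006 on both sides.

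**Bonferroni width.** 0.05/114 = 0.00044 gives z ≈ 3.52; 0.05/228 = 0.00022 gives z ≈ 3.70.

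**The case against.** The best defence is that overtesting is undefined and may only mean overfitting, which out-of-bag error does address. This does not stand: the Aim 1 section already credits the forest with reducing overfitting, in that word, and the Aim 2 sentence claims something further and sits just before an interval rule used for testing. It is also true that the rule is reported from cited work and that Aim 2 is largely a ranking question. Even so, the rule is the only criterion offered for calling a predictor reliable, and the hypothesis is phrased in its terms.

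Other objections do stand, and they limit the point. A reader might infer any of the following, which the document does not support:

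- *Several null predictors will certainly be reported.* That needs most predictors to be null and the intervals to be calibrated. The article establishes neither, and it argues from the literature that stress and motivation are consistent predictors.
- *The stated hypothesis is likely to be falsely supported.* The 94% to above 99.9% figures describe any flag anywhere. A hypothesis required to hold in every coaching arm is much harder to meet by chance, as the working shows.
- *The arms are small, so chance differences between Aim 2 lists will pass as coaching-specific effects.* The participants section gives 226 + 222 = 448 full-coach couples and 145 + 143 = 288 in each of the other two levels; only the six-model branch falls to 143 to 226. Differences between coaching levels are the task of Aim 3, which has its own analysis and does not compare Aim 2 lists.

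**Conclusion.** The overtesting statement is wrong, and the per-variable rule beside it has no error control across about 114 intervals (or about 228 with six models). On calibrated intervals with nearly all predictors null, the expected number of false flags is about 3 or 6 counting positive VIMP only, and about 6 or 11 counting both sides. With a quarter to a half null it is about 0.7 to 2.9, positive side only. These sizes rest on the tally of 19 predictors, the assumed share of nulls and calibration of an unspecified interval method. The defect in the text does not depend on them. It should be corrected, but it does not show that any particular Aim 2 result, or the stress and motivation hypothesis, would be false.

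**What to change.** Delete the statement that bootstrapping overcomes overtesting. In the preregistration, which the procedure section says is still to come:

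- name the hypothesised stress and motivation measures as the primary family;
- control the false discovery rate within each outcome across predictors and models, or use Bonferroni-width intervals (z about 3.5 for 114);
- state how the VIMP intervals are formed, and the p values if a Benjamini–Hochberg procedure is used, because either adjustment relies on their tail calibration;
- label all other predictors exploratory.

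The cost is a few lines of text, and fewer predictors will be called reliable. The article reports that only completion rates have been analyzed so far, so the change can still be made before the VIMP results are seen.

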### This Study: Research Aims and Hypotheses

Given past research, this study has 3 aims. The first aim is to investigate how well we can predict the completion rates and changes in relationship satisfaction. As model evaluation has rarely been used in this area of research, no specific hypotheses have been posited. The second aim of this study is to document the most powerful predictors of treatment adherence and gains in relationship satisfaction within 3 different levels of coaching. More specifically, what are the most powerful predictors of treatment adherence and gains in relationship satisfaction in a full-coach condition (with 4 scheduled 15-minute phone calls), automated coach condition (where couples only receive emails), and a contingent coach condition (where couples only receive scheduled coach calls after displaying a pattern of nonadherence)? Although many of the findings in this area of research are inconclusive, 2 findings are relatively consistent: lower external stress and higher intrinsic motivation both predict treatment adherence and gains. Thus, we hypothesize that, regardless of coach assignment, lower external stress and higher intrinsic motivation will emerge as reliable predictors of better adherence to the web-based program and subsequent treatment gains. In the final aim of the study, we intend to use the information gathered in the first 2 steps to determine the most powerful predictors of between-group differences. More specifically, what baseline characteristics are indicative of a given couple’s adherence or gains in relationship satisfaction to couples assigned to the full-coach program compared with automated coaching, contingent coaching, or the waitlist control condition? As this area of research is relatively underdeveloped, no specific hypotheses will be posited.

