### Participants

A total of 226 couples were randomly assigned to the OurRelationship coach condition, 145 couples were assigned to the OurRelationship contingent coach condition, and 145 couples were assigned to the OurRelationship automated (ie, email only) condition. Similarly, 222 couples were assigned to the ePREP coach condition, 143 couples were assigned to the ePREP contingent coach condition, and 143 couples were assigned to the ePREP automated (ie, email only) condition. A total of 224 couples were assigned to the waitlist control condition. In total, 4 individuals from the OurRelationship coach condition, 2 from the OurRelationship contingent coach condition, and 2 from the OurRelationship automated condition asked to discontinue and have their data removed from the study. Furthermore, 3 individuals from the ePREP coach condition, 2 from the ePREP contingent coach condition, and 3 from the ePREP automated condition asked to discontinue and have their data removed from the study.

In total, 47.5% (1178/2480) of the sample identified as male, and 52.5% (1302/2480) of the sample identified as female. The average length of the relationship was 5.74 years (SD 5.18). Most of the participants reported belonging to an opposite-gender relationship (2318/2480, 93.47%), and a smaller percentage were in same-gender relationships (162/2480, 6.53%). Most participants identified as White non-Hispanic (1520/2480, 61.29%), fewer identified as Black (434/2480, 17.5%), White Hispanic (279/2480, 11.25%), Black Hispanic (28/2480, 1.13%), American Indian or Alaskan Native (23/2480, 0.93%), Asian (17/2480, 0.69%), Hawaiian or Pacific Islander (4/2480, 0.16%), and Biracial (86/2480; 3.47%); and 3.59% (89/2480) of participants belonged to a race that was not listed. Furthermore, 6.81% (169/2480) of participants did not have a degree or diploma, 12.3% (305/2480) had earned a general education diploma, 14.23% (353/2480) had completed high school, 8.23% (204/2480) had a technical or vocational certification, 22.54% (559/2480) had some college degree, 8.83% (219/2480) had graduated with an associate’s degree, 10.69% (265/2480) had a bachelor’s degree, and 2.38% (59/2480) had a master’s or advanced degree.

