#### Data Analysis Plan for Aim 3: Predicting Between-Group Treatment Outcomes

Assuming that the models from the previous aim have levels of prediction accuracy, each of the within-group models will be used to generate predicted outcomes for each couple’s likelihood of adhering to the program as well as their treatment gains, creating counterfactual estimates of program completion and treatment gains as if each couple in the data set completed each intensity and method of coach contact [14].

To do this, the within-group models built in aim 1 will be used to generate potential outcomes for each couple’s likelihood of adhering as well as their gains in a (1) full coaching, (2) automated coaching, and (3) contingent coach conditions. If, in aim 1, the interaction terms result in a better RMSE, models will be constructed based on treatment assignment (ie, OurRelationship or ePREP) and coach assignment (ie, full, contingent, or automated). The estimates between the conditions for each couple’s between-group treatment differences between the full and automated coaching conditions can be understood as:

where 
[figure not shown]
 is the between-group likelihood of treatment adherence or gains for couple x, *Ŷ*(*x, Full Coach*) is the within-group likelihood of treatment adherence or gains for couple x in the full-coach condition, and *Ŷ*(*x, Contingent Coach*) is the within-group likelihood of treatment adherence or gains for couple x in the contingent coach condition [14]. These hypothetical between-group outcomes will then serve as dependent variables in a second random forest to calculate VIMP, which will identify the most powerful predictors of between-group differences. After identifying the most powerful predictors using VIMP, a multiple regression model will be estimated using the reduced set of variables to aid in the interpretation of the main effects. This process will thereby help clinicians determine which couples should be assigned to which level of coach contact.

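### The Aim 2 rule for a reliable predictor gives no direction, so a variable importance interval wholly below zero would also be labelled reliable (minor)

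*Protocol article*

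**What the plan says.** The Aim 2 section of the protocol article (Data Analysis Plan for Aim 2) describes permutation importance as a method that "compares and averages the permuted prediction error with the original error resulting in VIMP". It gives no formula and no sign. It then says that recent studies have used out-of-bag estimates "to generate CIs to test whether a variable has a meaningful effect in predicting an outcome", and reports their criterion: "95% CIs that do not include zero will be assumed to have reliable predictors". This is the only numerical cut-off for VIMP in the article.

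The next step, worded the same way in the Aim 2 and Aim 3 sections, is: "After identifying the most powerful predictors using VIMP, a multiple regression model will be estimated using the reduced set of variables". The Aim 3 section uses VIMP in a second random forest. It mentions no confidence interval and adds no direction.

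The section on research aims and hypotheses uses the same term for the study's one hypothesis, that "lower external stress and higher intrinsic motivation will emerge as reliable predictors of better adherence" and of later treatment gains, whatever the coach assignment.

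**The concern.** An interval that excludes zero on either side is a sensible criterion for a regression coefficient, because a coefficient of either sign can be a real effect. VIMP is different. It measures how much prediction deteriorates when a variable is scrambled and does not carry the direction of an association. A variable that helps in either direction has a VIMP above zero. A value below zero means that out-of-bag error fell after scrambling, which is what noise variables do by chance. An interval wholly below zero is therefore no evidence of prediction at any confidence level, yet it satisfies the criterion as written.

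What is at stake is the meaning of the label. The article supplies no other definition of a reliable predictor, and the hypothesis depends on that term.

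**Working it through.** The article states no error rate for this rule, so there is no figure to reproduce. The check has two parts.

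**1. Logic.** Take VIMP = (permuted out-of-bag error) − (original out-of-bag error). This sign is the usual one and is an assumption here. Let the 95% interval be (L, U).

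- Rule as worded: reliable if L > 0 or U < 0.
- Evidence of predictive value: L > 0 only.
- The two differ exactly when U < 0.

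**2. Size.** Inputs from the article:

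- Candidate predictors, counted from the measures sections: 6 demographic ("Predictor variables include race, ethnicity, household income, age, gender, as well as identifying as a same-gender couple"), 7 relationship measures including baseline satisfaction, 4 of external stress, 2 of motivation; 6 + 7 + 4 + 2 = 19.
- Outcomes: 2 (completion, gain in satisfaction). Coaching groups if the programs are pooled: 3. Intervals: 19 × 2 × 3 = 114.
- Couples per pooled group: full 226 + 222 = 448; contingent 145 + 143 = 288; automated 145 + 143 = 288.

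*Nominal tail.* With perfectly calibrated 95% intervals, 2.5% of null predictors lie wholly below zero. If all 19 are null and independent, the chance of at least one in a model is 1 − 0.975^19 = 38%. The expected count is 114 × 0.025 = 2.85.

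*Simulation.* Permutation VIMP need not behave like a calibrated normal estimate, so two separately coded simulations were run. Each used 19 predictors, of which 2 were true and 17 null, with intervals of VIMP ± 1.96 SE from subsampling. Interval method, subsample size and effect sizes are assumptions.

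- Simulation A: n = 288 and 448, continuous and binary outcomes, subsamples of size √n, delete-d standard error, 30 data sets per scenario (510 null intervals each).
- Simulation B: n = 288, continuous outcome, subsamples of size n^0.75, 49 data sets (49 × 17 = 833 null intervals), two standard errors.

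| Case | Null interval wholly below zero | Expected labels, all 114 null | Expected labels, 17 of 19 null (102) |
|---|---|---|---|
| B, delete-d SE | 0.12% | 0.14 | 0.12 |
| B, subsampling SE | 1.08% | 1.2 | 1.1 |
| A, lowest scenario | 1.6% | 1.8 | 1.6 |
| Nominal | 2.5% | 2.85 | 2.55 |
| A, highest scenario | 3.1% | 3.5 | 3.2 |

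The rates in B rest on few events: 0.12% is 1 of 833 and 1.08% is 9 of 833. When no predictor had any effect at all, A gave 2.5% to 4.4%.

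*Share of false labels.* Wrong-direction intervals were 25% to 49% of all null predictors flagged in A. In B they were about half: 1.08 / (1.08 + 0.96) = 53% with the subsampling SE, and 0.12 / (0.12 + 0.12) = 50% with the delete-d SE.

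*Cost to true predictors.* In A, no true predictor had an interval wholly below zero when predictors were independent, and 1 of 60 did when they were correlated. Detection of predictors with a positive VIMP interval is the same under either rule.

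**The case against.** The best defence is that the wording is loose and the intent is clear. The article reports the criterion as a convention of cited work, and its stated purpose is to find variables that matter for prediction. In that setting most readers would take the interval to lie above zero, and few analysts would report a wholly negative importance interval as a key predictor. This stands to the extent that the article never says it accepts both directions; that is only what its words permit. It does not remove the point, because the sentence is the one criterion given, nothing elsewhere supplies a direction, and the article promises preregistration for accountability.

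Three stronger readings are tempting, and the article does not support them:

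- *Harmful variables are carried into the regressions.* Both regression steps select the most powerful predictors by VIMP. If that means rank, negative values come last and may never enter. The article does not say that the interval is the filter.
- *The same rule governs Aim 3.* The Aim 3 section mentions no interval, so this would be extrapolation.
- *A negative interval would confirm the hypothesis.* The hypothesis is directional and VIMP is not; the article leaves interpretation of main effects to the regression. The label alone would not establish support.

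It is also fair to object that the size is uncertain. The rate moves by more than an order of magnitude with the interval method. The simulated rates should not be carried over to 228 intervals in program-specific models, since those groups have 143 to 226 couples and were not simulated. Nor are all 19 predictors likely to be null: the stress and motivation measures were chosen on prior evidence.

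**Conclusion.** The point holds as a minor defect in a stated decision rule. As worded, the criterion gives a wrong label whenever a VIMP interval lies wholly below zero, and no other section corrects it. The conclusion assumes the usual sign of VIMP, which the article does not spell out.

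The effect is probably small: roughly 0.1% to 3% of null predictors, or from well under one to a few labels over 114 intervals if most predictors are null. Both simulations agree that such intervals make up a sizeable share of the false reliable labels, but the absolute count depends on an interval method that the article does not give.

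**What to change.** In the Aim 2 section, replace the criterion with a one-sided statement: a predictor is called reliable only if the lower limit of its VIMP confidence interval is above zero; an interval that includes zero or lies wholly below it means not reliable. State the sign of VIMP (permuted minus original error) in the same place. If intervals are also used in the Aim 3 VIMP step, apply the same rule there.

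The cost is a sentence or two in the article or the preregistration. It needs no new data or computation, and predictors with a positive VIMP interval are detected exactly as before.
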